## Abstract

**Introduction:**

Coronavirus disease 2019 (COVID-19) is the current global pandemic of which residual symptoms exhibited by post-acute, rehabilitating patients include fatigue, dyspnoea, and insomnia. Chinese medicine (CM) has been widely used in China to treat different stages of COVID-19. While there are a significant number of clinical studies suggesting its efficacy and safety in its use during acute stage, there are very few randomized controlled trials focusing on the rehabilitation stage. Liujunzhi Decoction and Shashen Maidong Decoction are frequently recommended by official clinical guidelines in China to treat COVID-19 patients in rehabilitation stage. This double-blind, randomized, placebo controlled study aims to evaluate the efficacy and safety of the combination of the two formulae [named “COVID-19 Rehab Formula (CRF)”] in treating COVID-19 residual symptoms (long COVID).

**Methods:**

Eligible subjects will be randomly divided into treatment group and control group in 1:1 ratio. Treatment group will receive CRF along with certain pre-defined CM according to symptoms for 8 weeks, while control group will receive equivalent packs of placebo for 8 weeks. Data in terms of Fatigue Severity Score (FSS), self-reported COVID-19 long term symptom assessment, the modified British Medical Research Council (mMRC) Dyspnoea Scale, EuroQol Five-Dimension Five-Level (EQ-5D-5L) Questionnaire, pulmonary function test and adverse events will be collected and analyzed by SPSS 24. Blood test on liver and renal functions will also be conducted as safety measures.

**Conclusion:**

This study will evaluate the efficacy and safety of CRF in the treatment COVID-19 residual symptoms in a scientifically rigorous design.

**Clinical trial registration:**

[ClinicalTrials.gov], identifier [NCT04924881].

## 1. Background

The first identification in patients with severe pneumonia was in Wuhan province, China in November 2019. A novel coronavirus was identified as the cause by Chinese authorities on 7 January 2020 and was temporarily named “2019-nCoV.” Coronaviruses (CoV) are a large family of viruses that cause illness ranging from the common cold to more severe diseases. A novel coronavirus (nCoV) is a new strain that has not been previously identified in humans. The new virus was subsequently named the “COVID-19 virus.” COVID-19 has spread rapidly and now affects all over the world. This is the greatest pandemic of modern times and has been declared a Public Health Emergency of International Concern by the WHO Director-General (1). On 11 March 2020, coronavirus disease 2019 (COVID-19) was declared a global pandemic by the World Health Organization (WHO). As of 5 June 2022, over 529 million COVID-19 confirmed cases were reported worldwide, with more than 6 million related death (2).

Most of the infected people will develop mild to moderate illness, for example fever, cough, tiredness and joint pain etc. For some older people, and those with comorbidities like cardiovascular disease, diabetes, chronic respiratory disease, and malignancy are more likely to develop serious illness (2).

Up to now, most frequently used therapies are corticosteroids, antiviral agents, antiviral/immunomodulatory drugs, serotherapy, anticoagulant and inflammation inhibitors (3). The medium and long-term problems experienced by survivors of COVID-19 after discharge from hospital include fatigue, breathlessness and joint pain (4). Studies reported that different kinds of residual symptoms were left after patient discharged from the hospital. More than eight-seven percent reported a persistence of at least one symptom, particularly fatigue and dyspnoea 4 weeks after post-discharge (5). Overall, more than fifty four percent of all female patients reported moderate or severe fatigue, compared to 30 percent of male patients. Moderate or severe dyspnoea was also more often reported by females than males when they were under intensive care (53.8 vs. 21.1%) but the proportions were similar in those who stayed in ordinary ward (24.2 and 20.0%) (4). Besides, thirteen percent of patients had gastrointestinal symptoms such as diarrhea, vomiting, loss of appetite, etc. A cohort study showed that some COVID-19 recovered patients suffered from the above symptom up to 6 months or more (6). In Hong Kong, our data showed that 26.7 suffered fatigue, 20% suffered dyspnoea and 23.3% insomnia which are residual symptoms 6 months after discharged from the hospital of our COVID-19 recovered patients (unpublished data).

Traditional Chinese Medicine (TCM) has a long history and played an important role in the prevention and treatment of several epidemic diseases. During SARS epidemic in 2003, the treatment of TCM has achieved remarkable therapeutic effect. Some recent studies have demonstrated that among the limited therapeutics, TCM plays an important role in halting the progress of the disease and promoting the recovery of patients in the absence of vaccines or targeted drugs (7). As early as of 17 February 2020, total number of confirmed COVID-19 cases treated by TCM had already reached 60,107 in China (8).

Many different types of TCM have been proposed to treat COVID-19, of which the most famous are “three medicines and three formulae”: Jinhua Qinggan Granule, Lianhua Qingwen Capsule/Granule, Xuebijing Injection; Lung Cleansing and Detoxifying Decoction, HuaShiBaiDu Formula and XuanFeiBaiDu Formula, which are mainly used for active COVID cases of different severity. Clinical and pharmacological studies have suggested their efficacy, safety, and possible mechanisms in treating different stages of COVID-19, either used along with conventional treatment or independently (9–14).

For residual symptoms seen in COVID recovered patients, such as fatigue, dyspnoea and insomnia, there are also studies suggesting that TCM may be helpful. For example, a meta-analysis of 11 studies has shown that using Chinese medicine interventions together with conventional treatment is more effective than using the conventional treatment alone in treating chronic fatigue syndrome (15). There are also meta-analyses that have shown similar conclusions for idiopathic pulmonary fibrosis (16) and insomnia (17).

Liujunzhi Decoction (LJZD) and Shashen Maidong Decoction (SSMDD) are classic Chinese medicine formulae that have been used in China for hundreds of years. LJZD is composed of six herbs, namely, Ginseng Radix Et Rhizoma, Atractylodis Macrocephalae Rhizoma, Poria, Glycyrrhizae Radix Et Rhizoma Praeparata Cum Melle, Pinelliae Rhizoma Praeparatum and Citri Reticulatae Pericarpium, while SSMDD of seven: Adenophorae Radix, Polygonati Odorati Rhizoma, Glycyrrhizae Radix Et Rhizoma, Mori Folium, Ophiopogonis Radix, Lablab Semen Album, and Trichosanthis Radix. Their combination is proposed as the intervention of this trial because, from the perspective of Chinese medicine, the residual symptoms of COVID-19 can often be seen as the manifestation of “lung-spleen qi deficiency” or “dual deficiency of qi and yin” (18, 19). LJZD and SSMDD are two of the classic formulae used to treat these two pathologies, respectively. In fact, among the 33 official COVID-19 clinical guidelines published in mainland China, 10 have recommended the use of LJZD, and 6 recommended SSMDD (or their modified versions) in the recovery stage of COVID-19. Modified LJZD and SSMDD are the two most frequently recommended formulae (20).

To date, there are very few clinical studies of using TCM to treat the residual symptoms of COVID-19 recovered patients. A multi-center observational study in Hong Kong has shown that individualized TCM treatments could facilitate resolution of clinical symptoms (including fatigue, cough, shortness of breath, post-meal fullness, and loose stool), improve lung functions, and lead to healthier CM body constitutions in COVID recovered patients (21). A randomized controlled trial comparing a Chinese medicine (Qingjin Yiqi granules) combined with standard rehabilitation treatments (SRTs) against SRTs alone has also shown that the CM granules could assist reduction in fatigue and breathlessness (22). However, there is still a lack of double-blind, placebo-controlled randomized controlled trials on the subject—a void this study aims to fill.

## 2. Hypothesis

The residual symptoms of COVID-19 recovered patients can be improved after taking Chinese medicine.

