## 3. Objectives

To evaluate the efficacy of using COVID Rehab Formula “CRF” (LJZD and SSMDD with variations) on the residual symptoms of COVID-19 recovered subjects.

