## 4. Study outcomes

### 4.1. Primary outcome

Improvement of residual COVID-19 symptoms of fatigue using Fatigue Severity Score (FSS) at week 8.

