## 5. Study design

This is a double-blind, randomized, placebo-controlled superiority trial. Eligible subjects will receive either “CRF” granules or placebo granules for 8 weeks followed by a post-treatment visits at week 12.

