### 6.1. Inclusion criteria

•Aged above 18.•Have fatigue and one more residual symptoms (e.g., dyspnoea, sleep disturbance, cough, loose stool, abdominal distension, loss of appetite, dizziness, etc.) at least 5 weeks after discharge.•Patients are diagnosed with “lung-spleen qi deficiency” and/or“dual deficiency of qi and yin” by a Chinese Medicine Practitioner.•Voluntary written consent.

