### 7.2. Baseline randomization visit

At randomization visit, eligible subjects will have medical consultation and assessment by registered Chinese medicine practitioners (CMPs) investigators. Vital sign will be assessed, medical history and concomitant medications will also be recorded. If the subject has a result of not detected or negative result of SARS-Cov-2 RT-PCR test of deep throat saliva/professional-administered combined nasal and throat swab, and negative medical and travel history related to COVID-19 within 72 h, subjects will be instructed to do a pulmonary function test using a designated spirometer and complete the questionnaires; however, performing deep throat saliva/professional-administered combined nasal and throat swab test and pulmonary function test are not mandatory. Subjects will be randomly assigned (in a 1:1 ratio) to receive 8 weeks of either “CRF” granules 23–42 g daily or placebo granules 23–42 g daily. CMP investigators will prescribe and dispense the study treatment accordingly.

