### 7.3. Follow-up visit

Subjects will return for follow-up at week 8 (±4 days), and followed by a post-treatment visit at week 12 (Table 1). Symptom assessment and other questionnaires will be done. Blood tests will be repeated as safety measures at week 8. Subjects will be arranged to have another SARS-Cov-2 RT-PCR test of deep throat saliva/professional-administered combined nasal and throat swab, and confirmed to have negative medical and travel history related to COVID-19 within 72 h before the pulmonary function test at week 8. Performing deep throat saliva/professional-administered combined nasal and throat swab test and pulmonary function test are not mandatory. Treatment compliance will be recorded and adverse events will be captured on a patient diary. A direct telephone line will be provided so that subjects can report any adverse events during office hours between scheduled visits. The subjects will be recommended to attend Emergency Department at the nearest hospital beyond office hours if deemed necessary. To monitor compliance, subjects will be asked to bring back all remaining packs of granules for counting. One time free consultation with 1 month Chinese herbal treatment will be provided to all subjects after completion of study to ensure the follow up visit compliance.

**TABLE 1 T1:** Study schedule.

Items	Screening	Treatment period		Post-treatment follow up
	≤7 days to 0 day	Day 0 (baseline)	Week 8 (±4 days)	Week 12 (±4 days)
Informed consent	X			
Eligibility	X	X		
Medical consultation and assessment		X	X	X
Medical history		X		
Concomitant medication		X	X	X
Blood for safety measures	X		X	
Deep throat saliva or nasopharyngeal swab for SARS-Cov-2 RT-PCR test	*X		*X	
AE/SAE assessment			X	X
Questionnaires		X	X	X
Pulmonary function test		^#^X	^#^X	
Administration of study drug		X	X	
	

*Subjects will have deep throat saliva or nasopharyngeal swab for SARS-Cov-2 RT-PCR test within 72 h before follow up visit but it is not mandatory.

^#^Pulmonary function test will be skipped if no deep throat saliva has been done and showed not detected or negative within 72 h.

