### 10.2. Statistical analysis

Baseline data (gender, age, and vital signs) will be descriptively summarized. Differences of measurement data between the groups will be assessed using *t*-test for normally distributed continuous variables and Wilcoxon signed rank test for non-normally distributed variables. Measurement data of different groups in each visit will be reported as mean ± standard deviation (SD). Intra-group comparisons between baseline and each visit will be conducted by using paired *t*-test (or Wilcoxon signed rank test). Comparisons between groups will be conducted by using an analysis of variance (ANOVA), with other confounding factors like multicenter character conducting the covariate analysis. Statistical analysis for the data which do not meet above conditions (e.g., non-normal) will be conducted with the use of non-parametric test. For laboratory parameters, Spearman’s coefficient correlation has been used for comparison with different parameters and one way ANOVA test for significant correlation between groups. Study flow chart and graphs will be presented over different study times.

All *p*-values and 95 percent confidence intervals are two-sided, and *p* < 0.05 is considered statistically significant. Statistical analyses will be carried out exclusively by an independent statistician. All analyses will be performed by using SPSS, version 24 (SPSS).

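### The trial is designed and sized for superiority over placebo, but its hypothesis is a before-after statement and section 10.2 does not say which test decides efficacy

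*Protocol article*

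**What the plan says.** Section 5 of the protocol article is explicit about the design: "This is a double-blind, randomized, placebo-controlled superiority trial". Allocation is 1:1, and section 10.1 sizes the trial at 58 completers, raised to 68 (34 per arm) for 15% drop-out.

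The hypothesis in section 2 is worded differently: "The residual symptoms of COVID-19 recovered patients can be improved after taking Chinese medicine". It names no comparator. The objective in section 3 ("To evaluate the efficacy of using COVID Rehab Formula") names none either. The primary outcome in section 4.1 gives a variable and a time point: "Improvement of residual COVID-19 symptoms of fatigue using Fatigue Severity Score (FSS) at week 8". Section 10.1 describes its 9 points first as a drop and then as a difference.

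Section 10.2 plans two kinds of test. One is within arm: "Intra-group comparisons between baseline and each visit will be conducted by using paired" t-tests, or signed rank tests. The other is a between-group ANOVA, with centre given as an example of a covariate. A single two-sided p < 0.05 rule covers all p-values. The section does not say which of the two decides the primary efficacy question, and it does not call the paired tests descriptive.

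**The concern.** A before-after hypothesis and a superiority design ask different questions. Patients are enrolled because they still have fatigue and another symptom "at least 5 weeks after discharge", and FSS is read again at week 8. Natural recovery, placebo response and regression to the mean can lower FSS over that time in both arms. A paired test in the CRF arm cannot separate these from an effect of CRF. Only the randomised comparison can.

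Of the planned tests, the paired test answers the printed hypothesis most literally. If the placebo comparison were null while the CRF arm fell significantly from baseline, the hypothesis as worded could be reported as supported. That reading would give up what the placebo arm was included to provide.

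**Working it through.** **Inputs from the protocol (section 10.1).** Difference 9 points, SD 12, two-sided alpha 0.05, power 0.80, 58 completers, 15% drop-out, 68 randomised.

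**Step 1: which question the sample size answers.**
- Two-arm, normal approximation: n per arm = 2 × 12² × (1.960 + 0.842)² / 9² = 27.9, so 28 per arm (56 in total).
- Two-arm t-test (noncentral t): 29 per arm gives power 0.801, hence 58 in total. This matches the stated figure exactly.
- Drop-out: 58 / 0.85 = 68.2, against 68 stated.
- One-sample paired calculation with the same inputs: n = [12 × (1.960 + 0.842) / 9]² ≈ 14.

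The stated 58 therefore belongs to the comparison with placebo. A within-arm test would have needed about 14 patients.

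**Step 2: how often a within-arm test is significant when CRF adds nothing.** Assume that both arms fall by the same mean amount d, so the true effect against placebo is zero, with 29 completers per arm. The protocol gives neither d nor the SD of within-patient change. I take SD of change = 12, which equals the plan's SD if baseline and week-8 scores correlate at 0.5: 12 × √(2 × (1 − 0.5)) = 12. The standard error of the mean change is 12 / √29 = 2.23. Power is the upper tail of a noncentral t with 28 df and noncentrality d / 2.23, counting only significant improvements. The other two columns come from simulation (40,000 trials per setting).

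| Common fall d | CRF paired test significant | Between-arm test significant | CRF paired significant, between-arm not |
|---|---|---|---|
| 3 | 26% | 5% | 23% |
| 4.5 | 50% | 5% | 47% |
| 6 | 74% | 5% | 71% |
| 9 | 97% | 5% | 93% |

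**Step 3: sensitivity to the SD of change.** For d = 6, the CRF paired test is significant in 93% of trials at SD 9 and in 55% at SD 15. The between-arm test stays at about 5% in every setting.

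The paired-test figures are its power to detect a real fall from baseline. They are not false-positive rates of the trial's comparison with placebo.

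**The case against.** The strongest reply is that the comparator is already there. Section 5 names a placebo-controlled superiority trial, the background presents the lack of such trials as the gap to be filled, section 10.2 includes a between-group comparison, and the sample size works only as a two-arm calculation. On this view section 2 is a loosely worded clinical statement, and ranking the tests can be left to a full protocol or analysis plan that is not shown.

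Much of this stands. A reader might infer that, under the plan, a significant fall in the CRF arm would itself establish efficacy, that the within-arm tests rank equally with the comparison against placebo, or that the trial's error rate is inflated. The protocol supports none of these. It nowhere makes the within-arm test decisive, it leaves the two kinds of test unranked, and the between-arm test holds its 5%. Section 4.1 is also not at fault, since an outcome entry may reasonably name only a variable and a time point.

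The size of any common fall is uncertain too. The background describes symptoms lasting six months or more, five weeks is a minimum interval, and there is no FSS entry threshold, so neither natural recovery nor regression to the mean can be quantified.

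What the reply does not remove is the printed hypothesis. Its wording does not match the declared design, and an analysis plan that ranks the tests would still leave it in place.

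**Conclusion.** The point holds as a defect of wording and of test hierarchy, not of design or sample size. The hypothesis can be met without any advantage over placebo, and section 10.2 adds paired significance tests without saying that efficacy rests on the between-arm comparison. The consequence is a risk of misinterpretation: a null comparison with placebo could be reported beside a significant CRF-arm improvement as if the hypothesis were supported.

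How often that pattern would arise depends on a common fall and an SD of change that the protocol does not state, so the percentages illustrate the risk and do not forecast it. The point deserves correction because the remedy is specific and nearly free.

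**What to change.** 1. Section 2: state that CRF reduces FSS at week 8 more than placebo.
2. Section 10.2: name the between-arm comparison of week-8 FSS, adjusted for baseline FSS (ANCOVA), as the sole basis for the primary efficacy conclusion. Baseline FSS is already collected with the day-0 questionnaires, and adjusting for it is a better method than the ANOVA now described, which does not name baseline FSS as a covariate.
3. Section 10.2: report within-arm changes descriptively, as mean change with 95% CI and no p-value.

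Section 4.1 may stay as it is. The cost is a few sentences. The sample size of 58 (68 with drop-out) is already a two-arm calculation, so it does not change, and neither do the visits or the treatment.

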## 3. Objectives

To evaluate the efficacy of using COVID Rehab Formula “CRF” (LJZD and SSMDD with variations) on the residual symptoms of COVID-19 recovered subjects.

## 4. Study outcomes

### 4.1. Primary outcome

Improvement of residual COVID-19 symptoms of fatigue using Fatigue Severity Score (FSS) at week 8.

### 4.2. Secondary outcomes

1.Self-reported COVID-19 Long Term Symptom Assessment at week 8.2.Improvement of fatigue using Fatigue Severity Score (FSS) at week 12.3.Change of modified British Medical Research Council (mMRC) dyspnoea scale to measure the improvement of dyspnoea at week 8 and 12.4.Change of EuroQol five-dimension five-level (EQ-5D-5L) questionnaire and it’s Visual Analogue Scale (VAS) to measure the quality of life at week 8 and 12.5.Improvement of pulmonary function FEV1, FVC, and FEV1/FVC ratio at week 8.6.Adverse events related to study treatment.

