#### 7.4.2. Self-reported COVID-19 long term symptom assessment

For the symptom questionnaire, participants will be asked to report newly occurring and persistent symptoms, or any symptoms worse than before COVID-19 development. The symptom assessment has 5 scale, from none to very severe.

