#### 7.4.3. The modified British medical research council (mMRC) dyspnoea scale

The mMRC scale is a five-category scale to characterize the level of dyspnoea with physical activity in which higher scores correspond with increased dyspnoea (6).

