## 8. Study intervention

### 8.1. Study treatments

The core study treatment, COVID Rehab Formula “CRF” is prepared in the form of mixed LJZD and SSMDD concentrated herbal granules with variations.

Essentially, the “CRF” consists of Ginseng Radix Et Rhizoma (renshen) 8 g, Atractylodis Macrocephalae (baizhu) 7.2 g, Rhizoma Poria (fuling) 7.2 g, Glycyrrhizae Radix Et Rhizoma Praeparata Cum Melle (zhigancao) 4.8 g, Glycyrrhizae Radix Et Rhizoma (gancao) 4 g, Pinelliae Rhizoma Praeparatum (fabanxia) 9.6 g, Citri Reticulatae Pericarpium (chenpi)7.2 g, Adenophorae Radix (nanshashen) 8 g, Polygonati Odorati Rhizoma (yuzhu) 8 g, Mori Folium (sangye) 4.8 g, Ophiopogonis Radix (maidong) 8 g, Lablab Semen Album (baibiandou) 8 g, and Radix Trichosanthis Radix (tianhuafen) 8 g.

For study subjects with the following symptoms, specified Chinese medicine will be added; fatigue: Astragali Radix (huangqi) 15 g; dyspnea or cough with sputum: Trichosanthis Pericarpium (gualoupi) 10 g, Fritillariae Thunbergii Bulbus (zhebeimu) 10 g, Armeniacae Semen Amarum (kuxingren) 10 g; sleep disturbance: Ziziphi Spinosae Semen (suanzaoren) 10 g, Indian Bread with Pine (fushen) 10 g and Margaritifera Concha (zhenzhumu) 10 g; loose stool: Plantaginis Semen (cheqianzi) 10 g, Artemisiae Scopariae Herba (mianyinchen) 15 g, and Coicis Semen (yiyiren) 10 g.

Granules will be used with the dosage equivalent to the raw herbs according to the manufacturer. One daily dose of which (weight 23–42 g) will be dissolved in hot water and administered while it is lukewarm. Study subjects will take 2 times daily, 1–2 packs in the morning and the other in the evening after meal. The placebo granules, made of starch and caramel with similar appearance, smell and taste to the CRF but contain no active constituents, will be taken by the patients in the placebo group in the same way as those in the treatment group.

Both treatment herbal and placebo granules will be produced by a manufacturer with a Good Manufacturing Practice (GMP) certificate.

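### The mMRC outcome is meant to show improvement of dyspnoea, but dyspnoea is not required at entry and no comparison among dyspnoeic patients or baseline mMRC adjustment is named, so the effect is diluted

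*Protocol article*

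**What the plan says.** All references are to the protocol article.

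- **Outcome (4.2).** The third secondary outcome is "Change of modified British Medical Research Council (mMRC) dyspnoea scale to measure the improvement of dyspnoea at week 8"; the sentence goes on to week 12. No restriction by baseline dyspnoea is attached.
- **Entry (6.1).** Patients must "Have fatigue and one more residual symptoms (e.g., dyspnoea, sleep disturbance, cough, loose stool, abdominal distension, loss of appetite, dizziness, etc". Fatigue is mandatory. The second symptom can be any of several, so a patient with fatigue and sleep disturbance, for example, meets this criterion without dyspnoea.
- **Scale (7.4.3).** mMRC is a "five-category scale to characterize the level of dyspnoea with physical activity in which higher scores correspond with increased dyspnoea". It therefore has a lowest category below which nobody can move.
- **Treatment (8.1).** The core formula is the base of active treatment for everyone in that arm. On top of it, "For study subjects with the following symptoms, specified Chinese medicine will be added", and one of these additions is triggered by "dyspnea or cough with sputum: Trichosanthis Pericarpium (gualoupi) 10 g" (with two further herbs).
- **Analysis (10.2).** "Measurement data of different groups in each visit will be reported as mean" and SD. Groups are compared by *t*-test or ANOVA, or non-parametrically, with covariates exemplified by centre. Neither a symptomatic subset nor baseline mMRC is mentioned.
- **Symptom questionnaire (7.4.2).** "The symptom assessment has 5 scale, from none to very severe". It covers newly occurring as well as persistent symptoms.

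**The concern.** The stated purpose of the mMRC outcome is improvement of dyspnoea, but the trial population is defined by fatigue. Patients in the lowest mMRC category at Day 0 carry no information on improvement. They also receive no dyspnoea-specific addition unless they have cough with sputum. Averaging them with dyspnoeic patients pulls the mean change towards zero in both arms and shrinks the difference between arms.

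The estimate then depends on case mix as well as on treatment. A null mMRC result could mean no effect on dyspnoea, or that few patients had dyspnoea, and the planned summary could not tell these apart. With about 29 patients per arm, chance imbalance in who is dyspnoeic at Day 0 adds noise, and the covariates named in 10.2 do not include the baseline score that would remove part of it.

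**Working it through.** **1. The plan's own figure.** Section 10.1 takes a difference of 9, SD 12, two-sided alpha 0.05 and power 0.80. The normal formula gives n per arm = 2 × (1.96 + 0.84)² × (12/9)² = 27.9, so 28. The *t*-test version gives 28.9, so 29 per arm and 58 in total. Allowing 15% dropout, 58/0.85 = 68.2, and the plan takes 68. The figure reproduces, but it concerns FSS only; no calculation is given for mMRC. Below, 29 per arm is used as the evaluable number.

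**2. Dilution.** Let p be the share above the lowest mMRC category at Day 0. Then

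all-patient difference = p × (difference in dyspnoeic patients) + (1 − p) × (difference in floor patients).

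Floor patients can only stay or worsen. If they worsen equally often in both arms, the second term is zero and the result is p times the effect in dyspnoeic patients.

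**3. What is known about p.** The article does not give it. Section 1 reports, from the authors' unpublished cohort, "26.7 suffered fatigue, 20% suffered dyspnoea and 23.3% insomnia which are residual symptoms 6 months after discharged from the hospital". If dyspnoea and fatigue were independent, the share of fatigued patients with dyspnoea would be 20%. If every dyspnoeic patient were also fatigued, it would be 20/26.7 = 75%. These values are illustrative and do not bound p in the trial: requiring a second symptom raises the share, and the trial recruits through clinics and advertising rather than from that cohort.

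**4. Illustration on the mMRC scale (assumed inputs).** 29 per arm; Day 0 grades 1/2/3 steps above the lowest category in 50%/35%/15% of dyspnoeic patients; improvement by one grade in 65% (active) versus 30% (placebo) of them; worsening by one grade in 5% of all patients. The difference in dyspnoeic patients is 0.65 − 0.30 = 0.35 grade. Power was obtained by simulation.

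| Share p | Dyspnoeic, of 58 | All-patient difference (grades) | Power, change, all patients | Power, change, dyspnoeic subset |
|---|---|---|---|---|
| 20% | about 12 | 0.20 × 0.35 = 0.07 | 10% | 18% |
| 50% | 29 | 0.50 × 0.35 = 0.175 | 25% | 38% |
| 75% | about 43 | 0.75 × 0.35 = 0.26 | 45% | 52% |

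Across repeat runs, and across *t*-test and Mann-Whitney, the all-patient powers are 10%, 25–28% and 44–47%, and the subset powers 14–19%, 37–39% and 51–57%. Comparing week-8 values instead of change, in all patients, gives only about 6–7%, 11% and 18–19%.

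**5. Check under different assumptions.** Take a standardised effect of 9/12 = 0.75 in symptomatic patients (borrowed from FSS), zero change in the others, and 29 per arm. Power is 0.81 at p = 1. At p = 0.75 the effect falls to 0.56 and all-patient power to 0.57–0.67, against 0.70 in the subset. At p = 0.5 the effect is 0.375 and power 0.30–0.47, against 0.52. The ranges reflect whether the SD is held constant or allowed to shrink with the zero changes. The pattern is the same: a proportionate loss of effect, with a moderate power gain from the subset.

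**The case against.** Several points on the other side stand.

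- **Analysis set.** Section 10.2 does not say that all patients are compared. That is the natural reading of a group comparison with no restriction, but a statistical analysis plan that is not shown could narrow it. What the article does fix is an outcome worded as improvement of dyspnoea in a population that need not have it.
- **The all-randomised effect is legitimate.** It answers what happens to mMRC in fatigued patients with another symptom, and it counts any prevention of worsening. A reader might infer that floor patients are uninformative and that the all-patient figure must understate any real effect; this goes too far, because they still inform on worsening. The all-randomised comparison should be kept.
- **Entry.** A reader might infer that fatigue alone qualifies. Section 6.1 requires a second residual symptom, which makes the 20% scenario pessimistic.
- **Treatment.** A reader might infer that patients without dyspnoea get nothing relevant to it. Everyone on active treatment gets the core formula, and the dyspnoea addition also goes to those with cough with sputum. A subset defined by mMRC therefore does not match the tailoring exactly.
- **Symptom questionnaire.** A reader might extend the criticism to every item. Section 4.2 names the assessment at week 8 without promising item-by-item tests of improvement, and 7.4.2 includes newly occurring symptoms, so patients without a symptom at Day 0 belong in it. The point carries over only if items are compared for improvement.
- **Power.** The gain is modest, and at a 20% share the subset has about six patients per arm. The main benefit is an estimate that can be interpreted.

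**Conclusion.** The point holds for mMRC. As worded, the article pairs an outcome about improvement of dyspnoea with a population in which dyspnoea is optional, and names neither a comparison among dyspnoeic patients nor an adjustment for baseline mMRC. The mean difference shrinks in proportion to the share without dyspnoea: by a quarter at p = 75% and by half at p = 50%. At 50%, illustrative power is about 25% in all patients and 38% in the subset.

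The proportional shrinkage rests on floor patients worsening equally in both arms. The power figures also rest on the assumed improvement rates, grade distribution and 29 evaluable patients per arm; none of these mMRC inputs is in the article, and p is unknown. Only secondary outcomes are affected. The FSS primary outcome is not, because fatigue is mandatory at entry. This is a change worth making, and not a threat to the trial's main conclusion.

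**What to change.** In 4.2 and 10.2, before unblinding:

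1. Pre-specify the between-arm comparison of mMRC change at weeks 8 and 12 among randomised patients above the lowest mMRC category at Day 0, adjusted for Day 0 mMRC, with confidence intervals. The set is defined by a baseline measurement, so the comparison remains randomised.
2. Keep the all-randomised mMRC comparison beside it, also adjusted for Day 0 mMRC. The adjustment reduces noise from baseline imbalance but does not by itself remove the dilution.
3. Report new onset or worsening by arm in the patients who start in the lowest category.
4. If single items of the symptom assessment are compared for improvement, do the same for each item among those reporting it at Day 0, as a descriptive analysis, so that no further series of small tests is added.
5. Report the number in each subset by arm.

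The cost is a paragraph of wording. The study schedule (Table 1) already collects the questionnaires at Day 0, week 8 and week 12. The downside is small numbers and wide intervals in the subset, which must be shown, so a null result there may still be inconclusive. Defining the subset only after seeing the data would look post hoc.
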